# Effect of aerobic exercise and low carbohydrate diet on pre-diabetic non-alcoholic fatty liver disease in postmenopausal women and middle aged men – the role of gut microbiota composition: study protocol for the AELC randomized controlled trial

**DOI:** 10.1186/1471-2458-14-48

**Published:** 2014-01-17

**Keywords:** Liver fat content, Glucose metabolism, Lipid metabolism, Gut microbiota, Metabonomics, Human, Clinical setting

## Abstract

**Background:**

Pre-diabetes and non-alcoholic fatty liver disease (NAFLD) are associated with an unhealthy lifestyle and pose extremely high costs to the healthcare system. In this study, we aim to explore whether individualized aerobic exercise (AEx) and low carbohydrate diet (LCh) intervention affect hepatic fat content (HFC) in pre-diabetes via modification of gut microbiota composition and other post-interventional effects.

**Methods/design:**

A 6-month randomized intervention with 6-month follow-up is conducted from January 2013 to December 2015. The target sample size for intervention is 200 postmenopausal women and middle-aged men aged 50–65 year-old with pre-diabetes and NAFLD. The qualified subjects are randomized into 4 groups with 50 subjects in each group: 1 = AEx, 2 = LCh, 3 = AEx + LCh, and 4 = control. In addition, two age-matched reference groups (5 = pre-diabetes without NAFLD (n = 50) and 6 = Healthy without pre-diabetes or NAFLD (n = 50)) are included. The exercise program consists of progressive and variable aerobic exercise (intensity of 60 to 75% of initial fitness level, 3–5 times/week and 30–60 min/time). The diet program includes dietary consultation plus supplementation with a special lunch meal (40% of total energy intake/day) which aims to reduce the amount of carbohydrate consumption (30%). The control and reference groups are advised to maintain their habitual habits during the intervention. The primary outcome measures are HFC, serum metabolomics and gut microbiota composition. The secondary outcome measures include body composition and cytokines. In addition, socio-psychological aspects, social support, physical activity and diet will be performed by means of questionnaire and interview.

**Discussion:**

Specific individualized exercise and diet intervention in this study offers a more efficient approach for liver fat reduction and diabetes prevention via modification of gut microbiota composition. Besides, the study explores the importance of incorporating fitness assessment and exercise in the management of patients with pre-diabetes and fatty liver disorders. If our program is shown to be effective, it will open new strategies to combat these chronic diseases.

**Trial registration:**

Current Controlled Trials: ISRCTN42622771.

## Background

Non-alcoholic fatty liver disease (NAFLD) is becoming the most common cause of chronic liver disease in the developing world, and occurs in 17-30% of the population in Western countries and 2-4% worldwide [1]. In China the prevalence of NAFLD is 10-30% and up to 75% among obese and type 2 diabetes (T2D) [2]. At the same time, the prevalence of pre-diabetes has increased about 5-15% annually in different parts of China [3-5]. The main causes of pre-diabetes and NAFLD are related to lifestyle change due to modernization and both of them are largely preventable by changing the lifestyle.

It has been known for decades that gut microbes play an important role in metabolic, physiological and immunological processes in the human body [5-7]. Recently, studies have shown that unbalanced gut microbiota composition, i.e. dysbiosis, is associated with obesity-related metabolic disorders [8], T2D [9] and cardiovascular diseases (CVDs) [10] as well as longevity [11]. In addition, gut-derived bacterial components and metabolites are possible contributors to the onset of inflammation and further hepatic insulin resistance (IR) since the liver gains a substantial amount of nutrient- and metabolite-rich blood through the portal vein which links it to gut [12]. Recent evidence suggests a role for the gut microbiota both in the etiology and progression of hepatic fat accumulation (HFA), which is a multifactorial phenomenon associated with central obesity and metabolic syndrome [13,14].

The gut bacteria affect an individual’s ability to utilize energy from diet and when unbalanced microbiota composition can sustain a condition of subclinical chronic activation of the immune system, or so called systemic low-grade inflammation (SLGI), inducing insulin resistance and enhancing the metabolic risk [15]. On the other hand, in vivo studies show that some viruses such as enteroviruses can affect the metabolic status by directly infecting the liver and pancreas, while others such as adenoviruses can induce SLGI by infecting adipose tissue and interacting with mucosal immune system [16-18].

It is known that physical activity activates stomach and bowel function by altering local circulation and affects intestinal mucosal immunity. Interestingly, recent animal studies have shown that physical activity and diet cause compositional changes in gut microbiota [19,20]. Another study has shown that life-long calorie restriction of both high-fat and low-fat diet, but not voluntary exercise, significantly changed the overall structure of the gut microbiota of C57BL/6 J mice [11]. However, this study did not detail the intensity and duration of the exercise. Thus the effect of exercise on microbiota is still largely unknown. The mechanism underlying the effects of exercise and diet on gut microbiota needs to be established. Finally, data from human studies, though sparse, suggests that exercise can reduce liver fat [21] and thus the benefits of exercise may be mediated, in part, by a reduction in hepatic lipogenesis [22].

### Objectives and hypothesis

The gut microbiota composition can be modified by exercise and diet. Therefore, changes in the level of physical activity and composition of diet may result in favourable changes in microbiota composition which could, in turn, be accompanied by reductions in liver fat content, thus improving glucose and lipid metabolism and insulin sensitivity. A six-month exercise and diet intervention is enough to induce re-patterning of microbiota composition. However, “healthy” gut microbiota composition needs persistent exercise and balanced diet. Subjects may relapse to an “unhealthy” gut microbiota composition after cessation of exercise and balanced diet.

Therefore, the purpose of this study is to investigate the gut microbiota composition of postmenopausal women and middle aged men with pre-diabetic NAFLD compared to healthy controls, and whether chronic but latent bacterial infections are more frequent in NAFLD subjects than in healthy subjects. In addition, we will determine whether aerobic exercise and low carbohydrate diet reduce liver fat content via modification of gut microbiota composition in postmenopausal women and middle-aged men.

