### Eligibility criteria

1. Inclusion criteria for intervention groups:

Men or women aged 50–65 years with fasting glucose between 5.6 to 6.9 mmol/or glucose between 7.8 to 11.0 mmol/L 2 hour after the intake of glucose (75 g), diagnosed as NAFLD by ^1^H MRS (liver fat >5%) [23] and by questionnaire that on-going or recent alcohol consumption is <21 drinks on average per week in men and < 14 drinks on average per week in women [24]; no chronic cardiovascular, serious musculoskeletal or gastrointestinal problems and not on extreme diets; and for women, serum follicle-stimulating hormone level greater than 30 IU/L and last menstruation more than 6 months ago but within 10 years.

2. Inclusion criteria for reference groups:

Reference group 1: Men or women aged 50–65years with fasting glucose between 5.6 to 6.9 mmol/L or glucose between 7.8 to 11.0 mmol/L 2 hours after intake of glucose (75 g), not be diagnosed to have NAFLD by ^1^H MRS (<5%), no chronic cardiovascular, serious musculoskeletal or gastrointestinal problems and not on extreme diets; and for women, serum follicle-stimulating hormone level greater than 30 IU/L and last menstruation more than 6 months ago but within 10 years.

Reference group 2: Men or women aged 50–65 years with fasting glucose below 5.6 mmol/L or glucose below 7.8 mmol/L after 2 hour in takes of glucose (75 g), no NAFLD by ^1^H MRS (<5%), no chronic cardiovascular, serious musculoskeletal or gastrointestinal problems and not on extreme diets; and for women, serum follicle-stimulating hormone level greater than 30 IU/L and last menstruation more than 6 months ago but within 10 years.

3. Exclusion criteria:

Body mass index (BMI) > 38 kg/m2; serious cardiovascular or musculoskeletal problems; diagnosed Type 1 diabetes and T2D; and mental illness.

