### Measurements procedures

1. Screening:

The purpose of the screening is to verify the eligibility of potential participants. The recruitment of participants will be done at Yangpu District Health Care Service Centres and the Department of Endocrinology, Shanghai Shidong Hospital Shanghai, China. The potential subjects will be selected from the outpatient pool of those who have records of ultrasound for evaluation of liver fat and fasting blood results for diagnosing diabetes from 2012 to 2013. Registered nurses from health care centers will first contact the potential subjects and invite them to a study information meeting. Detailed information of the objectives of the study, its nature and constraints, the anticipated risks and the expected benefits are given by the investigating physician of endocrinology and professor of sport medicine in the recruitment information meetings. When the screening consent form has been signed, patients will be asked to fill in a screening questionnaire to check their health and medication background as well as alcohol consumption, and to undergo a glucose tolerance test (blood draw after overnight fasting, followed by samples of 30 minutes and 2 hours after the intake of 75 g of glucose).

2. First visit of the Run-in Trial:

The run-in trial consists of an 8-week period during which the participants who are qualified in terms of the screening questionnaire will complete all of the forms and protocols required for successful entry to the 1-year study. The purpose of the run-in trial is to identify and exclude those individuals who cannot or will not fulfil the requirements of the study. This should decrease the dropout rate of the 1-year study. We anticipate that approximately 50% of potential participants will not complete the run-in trial with sufficient detail or completeness to be entered in the study.

In the first visit of the Run-in Trial, those subjects qualified by screening (subjects who have fasting glucose level between 5.6 and 6.9 mmol/L or after 2-h intake of glucose between 7.8 to 11.0 mmol/L are willing to participate in this study will be invited for further blood sample collection. In addition, the pre-diabetes and healthy reference groups will undergo the same procedure. During the first visit, the participants will receive an in-depth explanation of the 1-year study and informed consent for the intervention and follow-up study will be obtained in writing.

3. Second visit of Run-in Trial:

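### The alcohol limit is written for the NAFLD groups only, and the latent-infection question compares NAFLD with healthy subjects who also differ in glucose status

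*Protocol article*

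**What the plan says.** **Objective.** Objectives and hypothesis gives two descriptive questions before the intervention question. The first concerns the "gut microbiota composition of postmenopausal women and middle aged men with pre-diabetic NAFLD compared to healthy controls". The second asks "whether chronic but latent bacterial infections are more frequent in NAFLD subjects than in healthy subjects".

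**Groups.** The Abstract states that "The qualified subjects are randomized into 4 groups with 50 subjects in each group", all with pre-diabetes and NAFLD. It adds two non-randomized reference groups: "5 = pre-diabetes without NAFLD (n = 50) and 6 = Healthy without pre-diabetes or NAFLD (n = 50".

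**Eligibility.** For the intervention groups, the diagnosis of NAFLD rests on liver fat above 5% by spectroscopy and on a questionnaire showing that "on-going or recent alcohol consumption is <21 drinks on average per week in men", with 14 as the figure for women. Reference group 1 has the same glucose ranges ("fasting glucose between 5.6 to 6.9 mmol/L or glucose between 7.8 to 11.0 mmol/L 2 hours after intake of glucose") and must "not be diagnosed to have NAFLD by" spectroscopy. Reference group 2 has lower glucose limits and the same liver rule. Neither reference entry mentions alcohol, and nor do the exclusion criteria.

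**Data collected.** Under Measurements procedures, the screening questionnaire is used to "check their health and medication background as well as alcohol consumption".

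**Analysis.** Statistical methods names contrasts of the three interventions with the control group. It names none involving the reference groups.

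**The concern.** A comparison of people with and without a condition is informative about that condition only to the extent that the two sides were otherwise selected alike. Two features of the text depart from that.

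The first is alcohol. The NAFLD side is truncated at a weekly limit and the reference side is not. As written, a person who drinks above the limit but has liver fat below 5% can enter either reference group, including the one labelled healthy. If drinking is related to gut microbiota, endotoxin or metabolomic measures, the comparison carries that relation as well, and it could hide a difference or create one.

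The second is wording. The latent-infection question is put as NAFLD against healthy, yet every NAFLD participant is also pre-diabetic and the healthy group is meant to be neither. The Discussion itself says it is unclear whether NAFLD arises from impaired glucose metabolism or the reverse, so the two should not be merged in a statement about NAFLD.

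Gut microbiota composition is listed among the primary outcomes, and these questions open the statement of purpose.

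**Working it through.** **Step 1. Set the criteria side by side (Eligibility criteria).**

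| | Intervention groups | Reference group 1 | Reference group 2 |
|---|---|---|---|
| Planned n | 4 × 50 = 200 | 50 | 50 |
| Liver fat | >5% | <5% | <5% |
| Fasting glucose (mmol/L) | 5.6-6.9, or 2-h criterion | 5.6-6.9, or 2-h criterion | <5.6, or 2-h criterion |
| 2-h glucose (mmol/L) | 7.8-11.0 | 7.8-11.0 | <7.8 |
| Alcohol limit per week | <21 men, <14 women | none | none |

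- NAFLD versus Reference group 1: liver fat and the alcohol rule differ; the glucose ranges are the same.
- NAFLD versus Reference group 2: liver fat, glucose status and the alcohol rule all differ.
- The alcohol asymmetry is in both contrasts, so changing the reference group does not remove it.
- The glucose difference from Reference group 2 is complete only by intent. Its two glucose limits are joined by *or*, so a person with one pre-diabetic value can qualify, which conflicts with the Abstract's description of that group.

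**Step 2. Match the questions to the groups.** The microbiota question names pre-diabetic NAFLD, which is what the intervention groups versus Reference group 2 measure. The latent-infection question names NAFLD alone, and its healthy comparator differs in two conditions.

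**Step 3. Precision of the baseline comparison.** The plan gives no figure for this comparison, so there is none to reproduce. In SD units, with the planned numbers:

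SE = √(1/200 + 1/50) = √0.025 = 0.158 SD.

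**Step 4. Possible alcohol bias.** Suppose a share q of references drink above the limit, this shifts an index by d SD, and the remaining references drink like the NAFLD participants. The bias is then q × d. The documents give neither value. Assuming q = 5-15% and d = 1 SD:

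- low end: 0.05 × 1 = 0.05 SD, or 0.05/0.158 = 0.32 SE
- high end: 0.15 × 1 = 0.15 SD, or 0.15/0.158 = 0.95 SE

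A smaller d reduces both in proportion.

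**Step 5. What a non-NAFLD shift would do.** Suppose NAFLD has no effect and some other difference between the groups (glucose or alcohol) shifts an index by b SD. The probability of a significant result in that direction at two-sided 0.05 is Φ(b/0.158 − 1.96), which is 0.025 when b = 0:

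| Assumed b (SD) | 200 versus 50 |
|---|---|
| 0.2 | 0.24 |
| 0.3 | 0.48 |
| 0.5 | 0.89 |

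These shifts are illustrations, not estimates. All of them exceed the 0.05-0.15 SD alcohol range in Step 4.

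**Step 6. Is the contrast with Reference group 1 usable?** The detectable difference at 80% power and two-sided 0.05, before multiplicity, is 0.158 × (1.960 + 0.842) = 0.44 SD. If 5-15% of 50 references were removed for alcohol, 47.5 to 42.5 would remain on average. The SE would be √(1/200 + 1/47.5) = 0.161 to √(1/200 + 1/42.5) = 0.169, and the detectable difference 0.45 to 0.47 SD.

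**The case against.** **The limit is part of the diagnosis.** It establishes that a fatty liver is non-alcoholic, so it has no diagnostic role where liver fat is below 5%. This explains how the asymmetry arose. It does not remove its effect, since drinking is still restricted on one side only.

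**Alcohol is recorded at screening, so the analysis can deal with it.** This stands in part. Recording makes repair possible, but the article states no threshold for references.

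**No passage says that alcohol affects microbiota or endotoxin.** This stands. The size of the harm cannot be taken from the documents, and a 1 SD shift is a large assumption. Even at the top of both assumed ranges, the bias is just under one standard error.

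**The design already separates glucose from liver fat.** This also stands. A reader might infer that no microbiota difference found in this study could be attributed to NAFLD, because every NAFLD participant is pre-diabetic. The documents do not support that. The microbiota clause names the combined condition and makes no claim about NAFLD alone, and Reference group 1 shares the glucose ranges of the intervention groups. The glucose point is therefore confined to the latent-infection clause. The assignment of each reference contrast to a question may sit in a full protocol or analysis plan that is not shown, so its absence from Statistical methods is not held against the article.

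**Reference group 1 does not isolate NAFLD either.** This is correct. The comparison is not randomized, the reference groups are described only as age-matched, and the Background itself links hepatic fat to central obesity.

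**Conclusion.** The point holds in two limited parts. First, the alcohol limit applies to the NAFLD groups and to neither reference group, so both reference comparisons are selected unequally on alcohol. This follows from the text and needs no assumption. Second, the latent-infection question is worded as NAFLD alone but uses a comparator that differs in liver fat and glucose status.

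How much the alcohol asymmetry matters is unknown. The 0.05-0.15 SD range rests wholly on the assumed q and d, and its direction is not known. The effect is at most modest under those assumptions, but the remedy is cheap. The reference comparisons are associational and will remain so after any change. The randomized comparisons of exercise, diet and their combination with control are untouched, because all four arms share the same criteria.

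**What to change.** 1. In Eligibility criteria, add to the entries for Reference groups 1 and 2 the alcohol limit already stated for the intervention groups, for the rest of recruitment (Trial status gives June 2014 as its end).
2. For references already enrolled, use the screening questionnaire either to restrict the baseline comparison to those under the limit or to adjust for intake. Fix the choice before the data are examined. If recruitment has closed, this step alone deals with alcohol.
3. In Objectives and hypothesis, base statements about NAFLD itself, including latent infections, on the intervention groups at baseline versus Reference group 1. Describe the contrast with Reference group 2 as pre-diabetes and NAFLD combined versus neither.
4. State that all reference comparisons are associational.

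**Cost.** One eligibility phrase and some rewording, with no new group or measurement. A few reference candidates are lost; under the assumed 5-15%, the detectable difference rises from 0.44 to at most 0.47 SD. The difference from Reference group 1 may be smaller than that from Reference group 2, and restriction or adjustment relies on self-reported drinking.

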## Methods/design

### Trial design

This is a six-arm study with four-arm randomized controlled trial and an additional 2 arms as references (Figure 1). Participants are recruited from the outpatient registration pool of those who have participated in annual health checks for diabetes and liver fat during 2012 to 2013 at the Yangpu District Health Care Service Centres, Shanghai, China. After an initial screening, potential subjects will be assessed for inclusion in the run-in trial. Those subjects who meet the inclusion criteria will be then invited to the intervention and follow-up study for a total duration of 1 year (6-month intervention and 6 month follow-up). Those participants who are qualified for the intervention study will be randomized into 4 groups after baseline assessments. Those subjects who are qualified for the reference groups will not be randomized.

**Figure 1 F1:**
[figure not shown]
Design of the AELC-study.

### Eligibility criteria

1. Inclusion criteria for intervention groups:

Men or women aged 50–65 years with fasting glucose between 5.6 to 6.9 mmol/or glucose between 7.8 to 11.0 mmol/L 2 hour after the intake of glucose (75 g), diagnosed as NAFLD by ^1^H MRS (liver fat >5%) [23] and by questionnaire that on-going or recent alcohol consumption is <21 drinks on average per week in men and < 14 drinks on average per week in women [24]; no chronic cardiovascular, serious musculoskeletal or gastrointestinal problems and not on extreme diets; and for women, serum follicle-stimulating hormone level greater than 30 IU/L and last menstruation more than 6 months ago but within 10 years.

2. Inclusion criteria for reference groups:

Reference group 1: Men or women aged 50–65years with fasting glucose between 5.6 to 6.9 mmol/L or glucose between 7.8 to 11.0 mmol/L 2 hours after intake of glucose (75 g), not be diagnosed to have NAFLD by ^1^H MRS (<5%), no chronic cardiovascular, serious musculoskeletal or gastrointestinal problems and not on extreme diets; and for women, serum follicle-stimulating hormone level greater than 30 IU/L and last menstruation more than 6 months ago but within 10 years.

Reference group 2: Men or women aged 50–65 years with fasting glucose below 5.6 mmol/L or glucose below 7.8 mmol/L after 2 hour in takes of glucose (75 g), no NAFLD by ^1^H MRS (<5%), no chronic cardiovascular, serious musculoskeletal or gastrointestinal problems and not on extreme diets; and for women, serum follicle-stimulating hormone level greater than 30 IU/L and last menstruation more than 6 months ago but within 10 years.

3. Exclusion criteria:

Body mass index (BMI) > 38 kg/m2; serious cardiovascular or musculoskeletal problems; diagnosed Type 1 diabetes and T2D; and mental illness.

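### The healthy reference group is defined with "or" between its two glucose limits, so people with one pre-diabetic value qualify for it and for the pre-diabetic reference group

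*Protocol article*

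**What the plan says.** The abstract (Methods/design) lists two age-matched reference groups of 50: group 5, with pre-diabetes but no NAFLD, and group 6, "Healthy without pre-diabetes or NAFLD". The section on randomization methods calls them Ref1 and Ref2, the latter being the healthy reference group.

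The Eligibility criteria set the glucose rules:

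- Ref1: "fasting glucose between 5.6 to 6.9 mmol/L or glucose between 7.8 to 11.0 mmol/L 2 hours after intake of glucose". The same limits, also joined by *or*, apply to the randomised arms and are repeated under Measurements procedures for the run-in.
- Ref2: "fasting glucose below 5.6 mmol/L or glucose below 7.8 mmol/L after 2 hour in takes of glucose".

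Ref1 and Ref2 otherwise have the same criteria: age 50–65, liver fat below 5% by MRS, the same health and diet conditions, and the same menopausal conditions for women. The only exclusion that concerns glucose is "diagnosed Type 1 diabetes and T2D; and mental illness".

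Under Trial design, the reference groups are not randomised. Under Objectives and hypothesis, one purpose is to compare the gut microbiota of people with pre-diabetic NAFLD with that of healthy controls. Gut microbiota composition is among the primary outcomes.

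**The concern.** Glucose is the only criterion that separates Ref1 from Ref2. If the glucose rule does not separate them, nothing else does. Membership is decided by eligibility and not by randomisation, and the article gives no rule of priority for a person who meets both definitions.

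As written, the Ref2 rule asks for one normal test, whereas the group's description requires two. People whom the protocol itself calls pre-diabetic may therefore be enrolled as healthy. If the outcome varies with glycaemic state, their presence would be expected to pull Ref2 towards the pre-diabetic groups and to blur the contrast between Ref1 and Ref2. The comparisons at stake are those that use the healthy group as the standard, including the microbiota comparison named in the objectives.

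**Working it through.** The article gives no figure to reproduce here, so this is a check of logic.

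**Inputs, all from Eligibility criteria.** Let F be fasting glucose and H the 2-hour glucose, in mmol/L.

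- Pre-diabetes (Ref1): F 5.6–6.9 or H 7.8–11.0.
- Ref2 as written: F < 5.6 or H < 7.8.
- Liver fat and all other criteria: the same for both groups.

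**Step 1: negation.** The negation of (A or B) is (not A and not B). Having no value in the raised range therefore means that F and H are both normal. The Ref2 rule joins the two normal limits with *or*, so it is not the complement of the pre-diabetes rule.

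**Step 2: all combinations.** Each test has three levels (normal, pre-diabetic range, above that range), which gives 3 × 3 = 9 combinations.

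| F | H | Ref1 | Ref2 as written | Both groups | Ref2 with *and* |
|---|---|---|---|---|---|
| < 5.6 | < 7.8 | no | yes | no | yes |
| < 5.6 | 7.8–11.0 | yes | yes | **yes** | no |
| < 5.6 | > 11.0 | no | yes | no | no |
| 5.6–6.9 | < 7.8 | yes | yes | **yes** | no |
| 5.6–6.9 | 7.8–11.0 | yes | no | no | no |
| 5.6–6.9 | > 11.0 | yes | no | no | no |
| > 6.9 | < 7.8 | no | yes | no | no |
| > 6.9 | 7.8–11.0 | yes | no | no | no |
| > 6.9 | > 11.0 | no | no | no | no |

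**Step 3: count.**

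- Ref2 as written: 5 of 9 combinations qualify.
- One of the five (both normal) fits the abstract's description.
- Two of the five have exactly one value in the pre-diabetic range and the other normal; these also meet Ref1. Examples are F 6.2 with H 7.0, and F 5.0 with H 9.0.
- The remaining two have one value above the pre-diabetic range. Whether they are removed depends on how the exclusion of diagnosed diabetes is read.
- With *and*: 1 of 9 qualifies for Ref2, and none qualifies for both groups.

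A person with both values in the pre-diabetic range does not meet Ref2 even as written. The misclassification that overlaps with Ref1 is confined to people with one pre-diabetic and one normal value.

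These are counts of combinations, not of people. The article does not say how common each combination is.

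**The case against.** The strongest reply is that this is a one-word slip in a condensed article. The abstract and the list of groups make the intent plain, and the description of the run-in treats the pre-diabetic and healthy reference groups as distinct. A physician and a researcher check each person's results against the inclusion criteria. The sample size statement and the intention-to-treat analysis concern the randomised groups only. Most of this stands, and it limits how serious the point is. It does not remove the point: the criteria that staff would apply carry the faulty wording, and nothing in the article corrects it.

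Four stronger readings are tempting, but the article does not support them.

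- **That the healthy group contains pre-diabetic people.** The text shows only that it permits them.
- **That a given amount of power is lost.** Suppose 10–40% of Ref2 were pre-diabetic and the group difference shrank in the same proportion. A comparison of 50 with 50 that has 80% power at 0.566 SD (two-sided 5% level) would then fall to between 71% and 39%. Both the share and the 80% baseline are assumptions; the article claims no power for reference contrasts. Shrinkage in full proportion also requires the misclassified people to have the mean of the comparison group. They have at least one normal glucose value and liver fat below 5%, so this is not shown, least of all for the comparison with NAFLD.
- **That the reference groups wrongly lack an alcohol limit.** The limit ("alcohol consumption is <21 drinks on average per week in men", with a lower one for women) is written as part of the NAFLD diagnosis. Its absence for people with liver fat below 5% contradicts nothing.
- **That the pre-diabetes rule simply admits diabetic values.** One value in range does qualify a person whose other value exceeds 6.9 or 11.0, but diagnosed diabetes is an exclusion. What remains unclear is whether a diabetic-range value found at screening counts as diagnosed.

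**Conclusion.** The point holds as an internal contradiction. The Ref2 criterion conflicts with the abstract's description of the group, and it lets Ref1 and Ref2 overlap in two of the nine combinations of results. This rests on the wording alone and needs no outside assumption.

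Its reach is limited to the non-randomised comparisons that use the healthy group, where misclassification can bias the result. Comparisons among the four randomised arms are untouched. The size of any bias or loss of power cannot be computed, because the article does not say how often exactly one of the two tests is abnormal. The correction is worth making, but the fault does not threaten the randomised trial.

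**What to change.** In the Eligibility criteria, Reference group 2, replace *or* with *and*, so that both fasting glucose < 5.6 mmol/L and 2-hour glucose < 7.8 mmol/L are required. This brings the criterion into line with the abstract.

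Re-check reference subjects already enrolled against their screening results. Move anyone in Ref2 with one value in the pre-diabetic range to Ref1, whose other criteria they already meet, or leave them out of the Ref2 comparisons.

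State also whether a diabetic-range value found at screening counts as diagnosed diabetes for the exclusion. This settles the combinations with one value above the pre-diabetic range.

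The cost is a one-word amendment and one clarifying sentence. No new test is needed, because fasting and 2-hour glucose are both part of the screening glucose tolerance test. Some reference subjects may have to be reclassified or replaced to keep 50 in Ref2. The Trial status section gives recruitment as continuing until June 2014, which leaves room for replacement if the change is made before then.
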